### Sampling

To date, no studies have reported on the use of combining such technologies, such as in the VirTele program so that this randomized, blinded feasibility trial will provide evidence for the effect size. However, as the first estimate of effect size, a sample size of 52 participants has been calculated using the Fugl-Meyer Upper Extremity Assessment as a primary outcome and G*Power 3.1 [16]. We assumed a medium effect size of 0.2, which was reported in a study with chronic stroke survivors with a 2-arm randomized clinical trial [17] and accounting for 20% retention issues (alpha=.05 and power=80%). This sample size corresponds to recommendations for pilot efficacy and feasibility trials [18] and is realistic, given time and budgetary constraints as well as recruitment potential. Thus, for the randomized, blinded feasibility trial, 52 participants will be recruited and randomly allocated to the experimental (n=26) or control group (n=26). A block randomization with a block size of six will be used, given time and material constraints.

For the multiple case study component, four therapists and the first 10 participants from the experimental group will be invited to participate in interviews. However, the final sample size of the participants diagnosed with stroke will be adjusted depending on the qualitative data saturation [19].

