**Scientific**		
	Safety	Occurrence of adverse events (pain, falls, motion sickness, dizziness, exertion, fatigue, and headaches) will be documented by a computerized participant log
	Satisfaction	With the technology: the Modified Short Feedback Questionnaire [36] With the interaction between the therapist and the participant: Health Care Climate Questionnaire (Perceived Autonomy Support) [37]
	Size of sample	The calculation will be done from the size of the treatment effect or the variance of the treatment effect

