### Data Analysis

#### Quantitative Data Analyses

Statistical analysis of the quantitative data will be performed using the Statistica software. Descriptive statistics will be used to report sociodemographic characteristics of participants (age, gender, handedness, and stroke characteristics) in both groups (experimental vs control). To address the first objective of the randomized, blinded feasibility trial, a mixed model approach will be applied for primary and secondary outcomes measure. Each model will contain one between-subject effect factor (group: control vs experimental), one within-subject effect factor (time: T1, T2, T3, and T4), and two covariates (gender and age) factors, which may impact exergame use. For each outcome measures, residual plots will be examined to verify normality and identify the best covariance structure. All the outcomes measure changes will be compared with the minimal clinically important differences. The effect size of the comparison between experimental and control groups will be calculated to estimate the final sample size. To address the second objective of the randomized, blinded feasibility trial, descriptive statistics (frequencies, means, and standard deviations) will be used to highlight the amount of exercise performed, the occurrence of adverse events, and participant and therapist satisfaction level in the experimental and control groups.

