### Data Collection

Participants will be recruited from different sites to increase the representativeness of the target population in the region. The control group will not receive any motivational interviewing or follow-up to keep the standard aspect of therapy that corresponds most to the clinical reality. This will enable us to identify the added value of the VirTele program compared with GRASP. After outcome measures collection in T1 and T2, to compare the effect of each intervention within and between groups, we will collect additional measures at T3 and T4 to evaluate the retention of gains.

The multiple case study provides an in-depth description of stakeholders use experience and potential use of VirTele program. In this study, we will have two case groups: participants diagnosed with stroke and study therapists (physical therapists or occupational therapist). Each of these cases experiences the intervention differently, and it is therefore essential to report them through interviews. The variation of the cases makes it possible to increase the variation of the experiences and thus to increase the robustness of the qualitative results [19]. UTAUT and SDT will serve as a basis for establishing certain links between the concepts that will emerge (Multimedia Appendix 1).

The results of this study will allow to verify if all elements of the protocol work well together to conduct a broader future study. We have tried to provide as much detail as possible about the various processes and steps of the protocol to facilitate its reproduction by other studies that seek to develop tools for the remote management of chronic diseases.

This project will also provide preliminary evidence of the efficacy of VirTele on motor and functional recovery of the UE following chronic stroke for future guidelines review, although studies caution us about solely using results from feasibility studies to establish intervention efficacy [35].

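### The larger trial is to be sized from this pilot's observed effect (Table 1 also allows its variance); about 21 completers per arm cannot support that.

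*Protocol article*

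**What the plan says.** Two places in the protocol article say how the later trial will be sized.

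- Data Analysis, Quantitative Data Analyses: "The effect size of the comparison between experimental and control groups will be calculated to estimate the final sample size". No confidence limit, shrinkage or target difference is attached to this step.
- Table 1, Scientific indicators, sample-size row: "The calculation will be done from the size of the treatment effect or the variance of the treatment effect". The row does not say which of the two will be used, or when.

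Other sections give the context. Sampling says the trial is meant to supply evidence on the effect size, and the Quantitative Data part of Data Collection names planning a larger trial as a purpose. The analysis section mentions minimal clinically important differences, but only as a yardstick for observed changes. The Discussion notes, of its efficacy evidence, "although studies caution us about solely using results from feasibility studies to establish intervention efficacy".

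**The concern.** The required sample size varies as 1/d², so sampling error in the observed d is magnified when it is put into a sample-size formula. An estimate 43% too high halves the computed size. A pilot of this size often misses by that much. An estimate that is too low, or has the wrong sign, gives an unaffordable size or none at all.

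Sizing the next trial is a declared output of this study, listed as a scientific feasibility outcome. If the rule in the analysis section is followed, that output could send a seriously underpowered trial forward, or discourage one that was worth running. The two statements of the rule also differ, so a reader cannot tell which will be applied.

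**Working it through.** **Inputs from the article (Sampling).** 52 randomised, 26 per arm; alpha 0.05; power 80%; 20% loss. Sidedness is not stated; two-sided is assumed here.

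**The plan's own figure.** The article calculated 52 "using the Fugl-Meyer Upper Extremity Assessment as a primary outcome and G*Power 3.1", and states "We assumed a medium effect size of 0.2" without naming the metric. A repeated-measures ANOVA interaction calculation with f = 0.2, 2 groups, 3 measurements and correlation 0.5 (the last two not stated) gives N = 42, and 42/0.8 = 52.5. So 52 can be approximately reproduced, but only with unstated inputs. What matters below is the number of completers: 26 × 0.8 = 20.8, about 21 per arm.

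**Precision of the observed effect.** SE(d) = √(2/n + d²/(4n)). With n = 21 and d = 0.4: √(2/21 + 0.16/84) = √(0.0952 + 0.0019) = 0.31. The 95% half-width is 1.96 × 0.31 ≈ 0.61. An observed d of 0.5 has a 95% CI of about −0.12 to 1.11.

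**Implied size.** n per arm = 2 × (1.96 + 0.84)²/d². An observed 0.5 gives 63 per arm. The upper limit of its interval gives 13, and the lower limit gives no finite number.

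**Consequence for the follow-on trial.** If it is sized at 80% power on the observed d, its real power is about Φ(2.80 × d_true/d_obs − 1.96). That is below 50% when d_obs exceeds 2.80/1.96 = 1.43 times the true d. With d_obs·√(n/2) following a noncentral t on 40 df (n = 21), the chances are:

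| Assumed true d | Needed per arm (normal formula) | Follow-on power < 50% | Estimate ≤ 0 |
|---|---|---|---|
| 0.2 | 392 | 39% | 26% |
| 0.4 | 98 | 30% | 10% |
| 0.5 | 63 | 25% | 5% |
| 0.8 | 25 | 16% | 0.5% |

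At true d = 0.4, power is below 60% in 37% of pilots, and the quartiles of the implied size run from about 41 to 424 per arm (counting non-positive estimates as no finite size).

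**Role of pilot size.** The computed size falls short of the need in about 50% of pilots at 21, 26 and 100 per arm alike. The depth of the shortfall does depend on pilot size: at true d = 0.5, power below 50% occurs in 25% of pilots with 21 per arm and about 7% with 100.

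**Alternative: fixed target, SD from the pilot.** With 40 df the 95% limits for the SD are √(40/59.34) = 0.82 and √(40/24.43) = 1.28 times the estimate. For a fixed target difference, follow-on power for that target is below 50% in about 0.3% of pilots and below 60% in about 3%. Power below 80% still occurs in about 53% (the chance that the pilot SD is too low, before rounding n up). Using the 80% one-sided upper limit, √(40/32.34) = 1.11 times the SD, lowers this to 20%.

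**The case against.** The strongest reply is that the plan is not firmly committed to the observed effect. Table 1 permits the variance route, which is close to the remedy; this is a condensed article; and any later trial must justify its own size, so the choice can be corrected after data collection. The *or* in Table 1 is real, and for that reason the point is partly one of reconciling two statements. But the analysis section states a rule, not a gap, and names only the effect size.

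The figures also rest on assumed true effects and a plain two-group comparison, whereas the plan specifies a mixed model over T1 to T4. This stands as a limit on the numbers. With an assumed T1–T2 correlation of 0.5 to 0.8, a raw d of 0.4 becomes 0.4/√(1 − r²), about 0.46 to 0.67. The SE of the adjusted effect stays near 0.31, and the chance of a non-positive estimate falls from 10% to about 7% to 2%. The problem shrinks but does not go away.

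A reader might infer more than the documents support:

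- *That 21 per arm is why the follow-on would be undersized about half the time.* It is not. Any nearly median-unbiased point estimate does this at any pilot size, and a pilot SD without an upper limit does much the same.
- *That the planning value is biased upward because only a favourable result leads to a larger trial.* No go/no-go rule on the effect is stated. The article ties the larger trial to feasibility and to whether the protocol elements work together.
- *That the Discussion contradicts the sizing rule.* Its caution concerns establishing efficacy; it bears on sizing only by analogy.

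**Conclusion.** The point holds in this form: the analysis section sizes the later trial from an observed effect whose 95% CI is about ±0.61, and Table 1 states the rule differently. Across assumed true d of 0.2 to 0.8, between 39% and 16% of pilots would yield a follow-on trial with under 50% power, and between 26% and 0.5% would yield no usable size.

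These figures assume 21 completers per arm, two-sided alpha of 0.05, 80% target power and a two-group standardised difference. The true effects are illustrative, since the article gives neither an SD nor an expected difference in Fugl-Meyer points.

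It might be tempting to treat this as a flaw that invalidates the trial. It does not touch randomisation, outcome assessment or this trial's own estimates; the consequence falls on the next trial. The severity is moderate.

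**What to change.** Reword the analysis section and the sample-size row of Table 1 so that they state the same rule:

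1. Size the larger trial on a prespecified, justified between-arm target difference in the Fugl-Meyer score. The minimal clinically important differences the plan already uses could inform it. They now serve to judge observed changes, so the target must be stated and justified as a difference between arms.
2. Take only nuisance parameters from the pilot: the Fugl-Meyer SD with an upper confidence limit (for example the 80% one-sided limit, about 1.11 × SD), the T1–T2 correlation and retention.
3. Report the pilot effect with its confidence interval as context, not as the planning value.

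The cost is a few sentences. The article reports one participant completed and no analysis begun, so at that stage the rule could be settled before results are seen. Recruitment, visits and treatment do not change. The downside is that the follow-on trial may be larger than an optimistic pilot estimate would suggest; the SD limit alone adds about 24% (1.11² ≈ 1.24).

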#### Qualitative Data Analyses

For the qualitative data, thematic analysis will be conducted for each case group. Transcripts will be coded using a predetermined coding scheme (Multimedia Appendix 1) based on the conceptual frameworks as well as other codes emerging from the data using NVivo software, and then codes will be grouped into overarching themes. To ensure the scientific rigor of qualitative data, the principles of Lincoln and Guba [39] will be applied. Audit trail and verification by members will be done to respect confirmability. A debriefing (external verification) will be applied to ensure credibility. Reliability will be achieved with verification by two coders of a part of the data. Transferability will be assured by taking reflexive notes and a detailed description of the context of the intervention. During the analysis, the results of the qualitative and quantitative data will be compared to help explain findings.

## Results

We expect to (1) collect preliminary efficacy data of this technology on the functional and motor recovery of the UE, following a stroke; (2) collect feasibility data with users at home (adherence, safety, and technical difficulties); and (3) identify the obstacles and facilitators for the technology use and understand the shared decision-making process during the VirTele program.

At the time of this manuscript submission, data collection was ongoing with one participant who had completed the study (experimental group) and used VirTele for 2 months [40] (Multimedia Appendix 2). At this stage of the study, we have not yet started the data analysis.

## Discussion

### Study Design

This paper describes the research protocol for a mixed method study, including a randomized, blinded feasibility trial with an embedded multiple case study. The aims of this study are to (1) determine the preliminary efficacy of VirTele on UE motor recovery, function, quality of life, and motivation in participants with chronic stroke, compared with conventional therapy (GRASP); (2) examine the feasibility of using VirTele with participants diagnosed with chronic stroke at home; and (3) identify the obstacles and facilitators for the technology use by participants diagnosed with stroke and stroke therapists and understand the shared decision-making process.

We have chosen a mixed study design because the use of both qualitative and quantitative approaches makes it possible to construct a more complete image of the studied phenomenon. The combination of the two methodologies should be approached not from the point of view of their differences but from the complementarities they can bring to the study [41]. If the feasibility trial examines the content of the intervention to see if it is effective and feasible, the qualitative approach examines the context of the intervention to see if it can be accepted and applied in clinical practice and explain some of the quantitative findings [42]. Feasibility trials are important to ensure that larger randomized clinical trials are rigorous and feasible and economically justifiable [13].

### Data Collection

Participants will be recruited from different sites to increase the representativeness of the target population in the region. The control group will not receive any motivational interviewing or follow-up to keep the standard aspect of therapy that corresponds most to the clinical reality. This will enable us to identify the added value of the VirTele program compared with GRASP. After outcome measures collection in T1 and T2, to compare the effect of each intervention within and between groups, we will collect additional measures at T3 and T4 to evaluate the retention of gains.

The multiple case study provides an in-depth description of stakeholders use experience and potential use of VirTele program. In this study, we will have two case groups: participants diagnosed with stroke and study therapists (physical therapists or occupational therapist). Each of these cases experiences the intervention differently, and it is therefore essential to report them through interviews. The variation of the cases makes it possible to increase the variation of the experiences and thus to increase the robustness of the qualitative results [19]. UTAUT and SDT will serve as a basis for establishing certain links between the concepts that will emerge (Multimedia Appendix 1).

The results of this study will allow to verify if all elements of the protocol work well together to conduct a broader future study. We have tried to provide as much detail as possible about the various processes and steps of the protocol to facilitate its reproduction by other studies that seek to develop tools for the remote management of chronic diseases.

This project will also provide preliminary evidence of the efficacy of VirTele on motor and functional recovery of the UE following chronic stroke for future guidelines review, although studies caution us about solely using results from feasibility studies to establish intervention efficacy [35].

### Conclusions

Extending rehabilitation following a stroke with remote services may be a promising strategy to overcome the limited resources in the health system. The VirTele program is a new approach that may provide stroke survivors continuous and remote access to rehabilitation services. This paper describes the protocol underlying the study of this technology to better understand how it can be used among different stakeholders and explore its preliminary efficacy in a chronic stroke population.

## Appendix

Multimedia Appendix 1 The predetermined qualitative coding scheme.

Multimedia Appendix 2 A screenshot of the combined use of Jintronix and Reacts.

Multimedia Appendix 3 Peer-review reports from the Canadian Institutes of Health Research - Part 1.

Multimedia Appendix 4 Peer-review reports from the Canadian Institutes of Health Research - Part 2.

## Abbreviations

GRASP: Graded Repetitive Arm Supplementary Program
SDT: self-determination theory
T1: at baseline
T2: at the end of 2-month intervention
T3: after a 1-month follow-up period
T4: after a 2-month follow-up period
UE: upper extremity
UTAUT: Unified Theory of Acceptance and Use of Technology
VirTele: program that combines virtual reality exergame and telerehabilitation application
